### Endpoints

#### Primary endpoint

The primary endpoint of the study is the 3-year DFS rate based on intention-to-treat analysis, which is defined as the proportion of patients who were alive without recurrence at 3 years from the date of surgery. It will be calculated using the time from the date of surgery to the date of recurrence detection, death, or the last follow-up. In cases where patients are lost before the 3-year mark, their data will be censored as of the last follow-up date and assessed accordingly.

#### Secondary endpoints

The secondary endpoints are the 3-year overall survival (OS) rate based on intent-to treat analysis, which is defined as the proportion of patients who are still alive 3 years from the date of surgery and calculated using the time from the date of surgery to the date of death or last follow-up; treatment-related toxicity according to the CTCAE (Common Terminology Criteria for Adverse Events) version 5.0; treatment discontinuation rate, defined as the proportion of participants in each arm who discontinued treatment because of toxicity or lack of compliance; and the percentage of the drug dose actually administered relative to the target drug dose. These secondary endpoints will provide valuable insights into the safety and tolerability of the adjuvant treatments compared in this study.

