**Methods:**

This multicenter, randomized (1:1), open-label, phase II trial will assess and compare the effectiveness and toxicity of mFOLFIRINOX and mFOLFOX 6 in patients with high-risk stage III colon cancer after radical resection. The goal of the trial is to enroll 312 eligible patients, from 11 institutes, aged between 20 and 70 years, with an Eastern Cooperative Oncology Group (ECOG) performance status of 0–2, or between 70 and 75 with an ECOG performance status of 0. Patients will be randomized into two arms - Arm A, the experimental arm, and Arm B, the reference arm - and will receive 12 cycles of mFOLFIRINOX and mFOLFOX 6 every 2 weeks, respectively. The primary endpoint of this study is the 3-year disease-free survival, and secondary endpoints include the 3-year overall survival and treatment toxicity.

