Personalized medicine is a crucial concept in the current treatment paradigm for metastatic colorectal cancer, and its extension to the management of non-metastatic colorectal cancer, particularly high-risk stage III CC, which carries high potential of progression to metastatic disease, is warranted. Therefore, it is essential to evaluate whether the triplet regimen of mFOLFIRINOX (oxaliplatin, irinotecan, and 5-FU), which has recently demonstrated superior efficacy in patients with unresectable metastatic colorectal cancer, can improve the prognosis of patients with high-risk stage 3 CC. Although a prospective single-arm study with a small sample size reported the safety and efficacy of triplet chemotherapy for locally advanced, resectable CC [12], and a randomized prospective study regarding a conventional regimen of triplet chemotherapy as an adjuvant treatment for high-risk stage III CC has been initiated in overseas [13], randomized controlled trials investigating the modified regimen of mFOLFIRINOX are lacking.

Therefore, the goal of this study is to evaluate the oncologic efficacy and safety of mFOLFIRINOX in comparison to those of the current standard of care, mFOLFOX 6, as an adjuvant treatment for patients diagnosed with high-risk stage III colon cancer after radical resection.

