### Interventions

#### Treatment and toxicity assessment

Patients will be randomized into two treatment arms - Arm A, the experimental arm, and arm B, the reference arm - and will receive 12 cycles of mFOLFIRINOX or mFOLFOX 6 every 2 weeks, respectively. The mFOLFIRINOX regimen consists of intravenous irinotecan 150 mg/m^2^, oxaliplatin 85 mg/m^2^, and leucovorin 400 (or levoleucovorin 200) mg/m^2^ on day 1 and continuous infusion of 5-FU 1200 mg/m^2^/d intravenously for the next 2 d (total 2400 mg/m^2^ over 48 h). The mFOLFOX 6 regimen consists of intravenous oxaliplatin 85 mg/m^2^, leucovorin 400 (or levoleucovorin 200) mg/m^2^, and bolus 5-FU 400 mg/m^2^ on day 1 and continuous infusion of 5-FU 1200 mg/m^2^/d intravenously for the next 2 d (total 2400 mg/m^2^ over 48 h).

Although there is no absolute contraindication with other treatments, caution will be exercised when co-administering these with drugs that might cause toxicities such as cardiotoxicity, hepatotoxicity, nephrotoxicity, myelodysfunction, and neurotoxicity. Toxicity will be monitored by taking the patient history and conducting laboratory tests before the initiation of the next cycle of treatment.

The drug dose could be adjusted at the discretion of the investigator, if necessary, because of toxicity, and the reduced dose could be sustained for subsequent cycles. Discontinuation will be considered after sustained toxicity despite dose reduction and management, recurrence during treatment, or on patient request.

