### Data management

To conceal personal information, the allocation sequence employs the double-digit participant number and the three-digit institute number, which are automatically generated on the eCRF in order of registered participants, based on the date of acquisition of informed consent. Access to the eCRF will be exclusively granted to registered researchers involved in this study. Screening, obtaining informed consent, enrollment, registration, and data collection will be conducted by investigators or qualified clinical research coordinators. Blinding will not be implemented because of the open-label nature of the study.

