Key inclusion and exclusion criteria	Inclusion criteria -Age between 20 and 70 years with an Eastern Cooperative Oncology Group (ECOG) performance status of 2 or lower, or age between 71 and 75 years with an ECOG performance status of 0 -Pathologically confirmed high-risk stage III CC (pT4N1-2 or pTanyN2) -Successful R0 resection for CC above the upper rectum within 60 d prior to screening -Adequate organ functions, as determined by laboratory tests after operation and before screening (Absolute neutrophil count ≥ 2 × 106 cells/mL, hemoglobin ≥ 9.0 g/dL, platelet count ≥ 100 × 106 cells/mL, alanine aminotransferase/aspartate aminotransferase ≤ 2.5 times the upper limit of normal (ULN), serum total bilirubin levels ≤ 1.5 times the ULN, alkaline phosphatase levels ≤ 2.5 times the ULN, serum creatinine levels ≤ 1.5 times the ULN or creatinine clearance > 50 mL/min based on the Cockcroft-Gault formula -Ability to understand and willingness to provide written informed consent -A life expectancy of at least 5 years Exclusion criteria -Presence of distant metastases -Lower and middle rectal cancer requiring radiotherapy -Postoperative complications of grade 4 or higher according to the Clavien-Dindo classification -Underlying medical or systemic conditions that impede chemotherapy administration -Known hypersensitivity to all relevant tests or treatment components -Familial adenomatous polyposis or hereditary nonpolyposis colorectal cancer -Inflammatory bowel disease -Presence of other incurable prior malignancies -Pregnancy (confirmed by serum beta-human chorionic gonadotropin test) or lactation Any other circumstances that, at the discretion of the investigator, might result in exclusion from the study
Study type	Multicenter, randomized (1:1), open-label, phase II trial
Date of first enrolment	June 2021
Target sample size	312
Recruitment status	Recruiting
Primary outcome(s)	3-year DFS rate based on intention-to-treat analysis
Key secondary outcomes	3-year overall survival (OS) rate, treatment-related toxicity

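### The only named adverse-event endpoint is limited to treatment-related toxicity in an open-label trial, which leaves the between-arm safety comparison open to differential attribution

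*Protocol article*

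**What the plan says.** The Background section of the protocol article makes safety a comparative aim: "the goal of this study is to evaluate the oncologic efficacy and safety of mFOLFIRINOX in comparison to those of the current standard of care". Under Secondary endpoints, the adverse-event measure is "treatment-related toxicity according to the CTCAE (Common Terminology Criteria for Adverse Events) version 5.0". In the WHO registration data set, the row for key secondary outcomes reads "3-year overall survival (OS) rate, treatment-related toxicity", so the same restricted measure is the only safety outcome there. The Methods part of the abstract is looser: "secondary endpoints include the 3-year overall survival and treatment toxicity".

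On who knows the arm, the Data management section says "Blinding will not be implemented because of the open-label nature of the study", and that "data collection will be conducted by investigators or qualified clinical research coordinators". On capture, the section on treatment and toxicity assessment says "Toxicity will be monitored by taking the patient history and conducting laboratory tests before the initiation of the next cycle of treatment". Table 1 schedules a safety assessment at every cycle.

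Secondary endpoints also lists two tolerability measures. One is the share of the target dose actually given. The other is the discontinuation rate, which counts patients who "discontinued treatment because of toxicity or lack of compliance". The Monitoring section adds checks of treatment completion and serious adverse event (SAE) rates at 20% and 40% of the sample, and reporting of SAEs to the ethics boards. It limits neither to related events.

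**The concern.** Randomisation protects a comparison of everything that happens to patients after allocation. It does not protect a comparison of a subset chosen by a judgement made after allocation with the arm known. Restricting the endpoint to related events puts such a judgement between the event and the count.

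There is room for that judgement to vary. Patients may enter screening up to 60 days after resection, and only postoperative complications of Clavien-Dindo grade 4 or higher exclude them. Early diarrhoea, infection or fatigue can therefore have a surgical explanation as well as a chemotherapy one. The Discussion section describes the conventional triplet as considerably more toxic than the modified one, so staff may hold expectations about the experimental arm. Ready attribution there would inflate the triplet's excess toxicity; ascribing events to surgery would hide part of it. The weighing of benefit against harm would inherit either error.

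**Working it through.** The plan gives no figure on this point to reproduce. The check has two parts.

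**1. Which safety measures depend on attribution**

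| Measure | Where stated | Needs a judgement of cause? | Stated secondary endpoint? |
|---|---|---|---|
| Treatment-related toxicity by CTCAE grade | Secondary endpoints; registration data set | Yes | Yes |
| Discontinuation for toxicity or non-compliance | Secondary endpoints | Yes, through the assigned reason | Yes, but counts stopping, not events |
| Share of target dose given | Secondary endpoints | No | Yes, but not an adverse-event measure |
| SAE rates at 20% and 40% of the sample | Data safety monitoring | No | No, a monitoring item |
| SAE reporting | Safety monitoring | No | No, a reporting duty |

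No row is both free of attribution and a between-arm adverse-event endpoint.

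**2. What unequal attribution could do**

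Let p be the all-cause rate of a given toxicity in an arm and a the share of those events called related. The reported rate is p × a. If p is the same in both arms, the reported difference is p × (a_A − a_B), which is zero only when the shares are equal.

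The inputs below are assumptions; the documents give neither p nor a. The sample is 156 per arm, from the sample size section, taken as all treated. The article states no test for toxicity, so a two-sided 5% test of two proportions is assumed. With p̄ the mean of the two reported rates, the chance of rejection is approximately

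Φ{ [Δ − 1.96 √(2p̄(1−p̄)/n)] / √([p_1(1−p_1) + p_2(1−p_2)]/n) }.

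| p, both arms | Related share, A v B | Reported, A v B | Spurious gap (points) | Chance of rejection |
|---|---|---|---|---|
| 30% | 90% v 80% | 27% v 24% | 3 | 9% |
| 30% | 95% v 75% | 28.5% v 22.5% | 6 | 23% |
| 40% | 90% v 80% | 36% v 32% | 4 | 11% |
| 40% | 95% v 75% | 38% v 30% | 8 | 32% |
| 50% | 90% v 80% | 45% v 40% | 5 | 14% |
| 50% | 95% v 75% | 47.5% v 37.5% | 10 | 43% |

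A worked row: for 38% v 30%, p̄ = 0.34, 1.96 × √(2 × 0.34 × 0.66/156) = 0.105, and √((0.38 × 0.62 + 0.30 × 0.70)/156) = 0.0534. Then (0.080 − 0.105)/0.0534 = −0.47 and Φ(−0.47) = 0.32.

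A lower rate with a wider split behaves alike: 20% × 0.90 = 18% against 20% × 0.70 = 14%, a gap of 4 points. With equal shares the gap is zero. The error can also run the other way: all-cause rates of 40% v 36% with related shares of 80% v 90% give 0.40 × 0.80 = 32.0% against 0.36 × 0.90 = 32.4%, and a real excess of 4 points disappears.

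**The case against.** A reader might infer that the whole safety comparison turns on attribution and says nothing of what happened to patients. The documents do not support that. The share of target dose given needs no judgement of cause, nor does overall survival, and the monitoring of SAEs is not restricted to related events. These measures temper the point. They do not remove it: dose can be adjusted at the discretion of an investigator who knows the arm, and SAE rates leave out non-serious toxicity.

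A reader might also take it as stated that an unblinded investigator decides relatedness for each event. The article does not say who decides, or how. The inference from an open-label design is reasonable, but it is an inference. The restricting word may even be ordinary shorthand for toxicity on treatment, as the abstract's wording suggests. Attribution procedures are commonly left to the full protocol, so their absence here is no fault. What the article does fix is the endpoint, and it fixes it with the restriction in two places.

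Three further arguments carry weight. Both arms receive oxaliplatin, leucovorin and infusional 5-FU, so much toxicity could be ascribed to chemotherapy in either arm, and laboratory-graded events leave less room for opinion. Complications within 30 days of surgery are recorded separately at screening, and 12 two-week cycles extend well past that period. Finally, no differential attribution has been shown; the rates in the table are assumed. All three limit the likely size of the problem, but none makes the related subset a comparison protected by randomisation.

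**Conclusion.** The point holds in a limited form. The one adverse-event endpoint that the article names is filtered by relatedness, in an unblinded trial that sets out to compare safety, and CTCAE grading does not remove that filter. Differential attribution is possible in either direction. The gaps of 3 to 10 points, and the rejection chances of about 9% to 43%, show what modest differences in attribution would do under the assumed inputs; they do not estimate what will happen in this trial. It would go too far to conclude that the triplet's toxicity will be overstated, or understated.

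The conclusion assumes that the restriction is meant literally and that whoever applies it knows the arm. The endpoint is secondary; the primary disease-free survival analysis and the sample size are untouched. The change is a worthwhile, inexpensive improvement and not the repair of an error that threatens the trial.

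**What to change.** In the Secondary endpoints section and in the key secondary outcomes of the registration data set, define the main safety comparison as all treatment-emergent adverse events by CTCAE version 5.0 grade, and all SAEs, by arm in treated patients regardless of attribution. Keep treatment-related events as a supplementary table, and use the same term in the abstract.

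The cost is a change of endpoint wording and an added table, since safety is already assessed at every cycle in both arms. It also requires that every event be entered on the electronic case report form whatever its cause. The article does not say whether this is done, so it should be checked, including for the 19 patients enrolled by July 2023.

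There are two downsides. Background postoperative events will raise the rates in both arms. And the change removes the attribution step only: eliciting and grading events will still be done by staff who know the treatment.

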### Randomization

Randomization will be adjusted based on the following stratification factors: pT1-3N2 versus pT4N1 versus pT4N2, and the right colon (from the cecum to the distal transverse colon above the splenic flexure colon) versus the left colon (from the splenic flexure colon to the rectosigmoid colon). This process will be conducted according to the special program on the electronic case report form (eCRF) webpage, and the result of randomization will be presented on the webpage immediately after the registration of patients. This eCRF, which includes the randomization program, was developed by the special department, the “Academic Clinical Research Operating Support System (ACROSS)” of the lead institute, which consists of data management and monitoring specialists that support investigator-oriented clinical studies. They are independent from the sponsor, and no competing interests will exist.

### Data management

To conceal personal information, the allocation sequence employs the double-digit participant number and the three-digit institute number, which are automatically generated on the eCRF in order of registered participants, based on the date of acquisition of informed consent. Access to the eCRF will be exclusively granted to registered researchers involved in this study. Screening, obtaining informed consent, enrollment, registration, and data collection will be conducted by investigators or qualified clinical research coordinators. Blinding will not be implemented because of the open-label nature of the study.

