## Methods

### Study design

This multicenter, randomized (1:1), open-label, phase II trial assesses the effectiveness and toxicity of mFOLFIRINOX compared to those of mFOLFOX-6 as an adjuvant treatment for patients with high-risk stage III CC. Patient enrollment will be performed across 11 tertiary hospitals in one country. The flow-diagram of the study is presented in Fig. 1.

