#### Recurrence assessment

Recurrent assessment, including carcinoembryonic antigen measurement, abdominopelvic computer tomography (CT), and chest radiography or CT, will be performed after every 4 cycles of treatment and postoperatively every 4 months for 2 years and every 6 months for the next 3 years. The modality and interval of evaluation could be added and adjusted at the discretion of the investigator, if necessary. If recurrence is detected during treatment, study treatment will be discontinued and a standard personalized treatment will be conducted. If recurrence is detected during the follow-up period, a standard personalized treatment will be conducted. The participant timeline is presented in Table 1.

**Table 1 Tab1:** Timeline of enrollment, intervention, assessment, and surveillance in FROST trial

Visit^1^	Screening	Chemotherapy period			Follow-up period	
		C1D1	C2–3D1 C5–7D1 C9–11D1	C4D1 C8D1 C12D1	F1–5	F6, F7
**Interval**			2 weeks (-4 d/+7 d)		4 months (-14/+30 d)	6 months (-14/+30 d)
Informed consent	X					
Screening number	X					
Complication check^2^	X					
Criteria check	X	X				
Randomization		X				
Performance status check	X	X	X	X		
Medical history and physical examination	X	X	X	X	X	X
Height, weight, BSA^3^		X	X	X		
Vital sign^4^	X	X	X	X		
Laboratory test^5^	X	X	X	X	X	X
Pregnancy test ^6^	X		X (even-numbered cycles)			
Treatment		X	X		X	
CEA^7^	X			X	X	X
Imaging study^8^				X	X	X
Colonoscopy^9^					X	X
**Safety assessment**		X	X	X		
**Efficacy assessment**				X	X	X

^1^The next visit is based on the previous visit date. In the treatment phase, the first day of each treatment cycle (e.g., C1D1, C2D1…) is the reference date

^2^Postoperative complications: Evaluate complications within 30 d after surgery according to the Clavien-Dindo Classification

^3^BSA (body surface area)

^4^Vital signs include blood pressure, heart rate, respiratory rate, and body temperature

^5^Laboratory tests include complete blood count, liver and kidney function tests, and electrolytes

^6^Pregnancy test (serum beta-human chorionic gonadotropin test): Performed on even-numbered cycles (C2, 4, 6, 8, 10, 12) only for fertile women

^7^CEA (carcinoembryonic antigen): The first test performed before surgery and during the postoperative screening period

^8^Imaging studies include abdominopelvic computed tomography (CT) and chest radiography (C4, C8, F2, F4, F6) or CT (C12, F1, F3, F5, F7)

^9^Colonoscopy is recommended in F1 and F7

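### Open-label treatment is given as the reason for no blinding at all, which leaves an avoidable risk of assessment bias in 3-year DFS

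*Protocol article*

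**What the plan says.** All of the following is in the protocol article.

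- **Data management:** "Blinding will not be implemented because of the open-label nature of the study". The sentence is unqualified and gives no other reason. The same section says that "data collection will be conducted by investigators or qualified clinical research coordinators".
- **Randomization:** "the result of randomization will be presented on the webpage immediately after the registration of patients".
- **Primary endpoint:** "The primary endpoint of the study is the 3-year DFS rate based on intention-to-treat analysis", defined as the proportion alive and free of recurrence 3 years after surgery. On timing: "It will be calculated using the time from the date of surgery to the date of recurrence detection, death, or the last follow-up".
- **Recurrence assessment:** the tools are listed as "Recurrent assessment, including carcinoembryonic antigen measurement, abdominopelvic computer tomography (CT), and chest radiography or CT". The section adds: "The modality and interval of evaluation could be added and adjusted at the discretion of the investigator, if necessary".

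Nowhere does the article exempt image readers, endpoint assessors or analysts from the no-blinding statement. It mentions no central review, endpoint committee or masked analysis.

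**The concern.** The article makes a decision and gives a reason for it, so this is not a detail that a condensed article has simply left out. The reason covers less than the decision. Two chemotherapy regimens given openly cannot be hidden from the patient or the treating team. The person who reports a CT or chest image gives no treatment, and nor does the person who analyses the data.

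Death needs no judgement. Recurrence on imaging sometimes does: an equivocal node, lung nodule or anastomotic lesion can be called now, called later or not called. If knowledge of the arm affects such calls, the 3-year DFS difference moves for a reason unrelated to disease. A shift towards Arm A raises the false-positive rate, and a shift the other way can hide a real benefit. Testing at the 10% level leaves limited room for added error.

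**Working it through.** **Step 1: does the stated reason support the stated decision?**

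| Who | Must know the arm because treatment is open? | Influence on 3-year DFS |
|---|---|---|
| Patient, treating investigator | Yes | Reporting of symptoms, requests for scans |
| Radiologist reporting scheduled imaging | No | Whether and when recurrence is called |
| Statistician fixing dates and analysis sets | No | Analysis choices, not scan reading |

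The reason covers the first row only.

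**Step 2: which errors reach the endpoint?** The endpoint is status at 3 years. A recurrence dated at month 20 instead of month 16 is still an event by month 36, so the 3-year proportion barely changes. The errors that count are a recurrence never called, a recurrence called falsely, and a call moved across month 36.

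**Step 3: how much would a given shift matter?** The plan states no figure for assessment error, so there is none to reproduce. Inputs from Sample size calculation are 156 per arm, 65% control DFS and a 10% significance level with sidedness not stated. The planned 156 is taken as given. The shift b is an assumption: a net 2 to 3 percentage points, all in favour of Arm A, with no true difference between arms.

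- Standard error under the null: √(2 × 0.65 × 0.35 / 156) = 0.0540, or 5.4 points.
- Critical difference: 1.645 × 5.40 = 8.9 points (two-sided 10%); 1.2816 × 5.40 = 6.9 points (one-sided 10%).
- Chance of falsely favouring Arm A: P(Z > z − b/0.0540).

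| Assumed shift b | Patients in one arm (b × 156) | Two-sided 10% | One-sided 10% |
|---|---|---|---|
| 0 | 0 | 5.0% | 10.0% |
| 2 points | 3.1 | 10.1% | 18.1% |
| 3 points | 4.7 | 13.8% | 23.4% |

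**Step 4: a second construction.** Allow for the planned 10% dropout (156 × 0.9 ≈ 140 per arm). Suppose that a share of the Arm A events is not called by 3 years, treating all 35% as recurrences. The standard error is √[0.65 × 0.35/140 + p(1 − p)/140], with p the shifted Arm A rate, at two-sided 10%.

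| Share not called | Patients | Spurious gain | Chance of falsely favouring Arm A |
|---|---|---|---|
| 5% | 2.5 | 1.75 points | 9.1% |
| 10% | 4.9 | 3.5 points | 15.3% |
| 20% | 9.8 | 7.0 points | 35.2% |

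Both constructions show that a few one-directional calls would be enough to double the one-tail error. Neither shows that such calls will occur.

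**Step 5: is a 2 to 3 point shift plausible from delay alone?** With a constant hazard and 65% DFS at 3 years, DFS at month 30 is 0.65^(2.5/3) = 0.698, so about 4.8% of patients have an event in months 30 to 36. Delay alone would have to push 2/4.8 ≈ 40% to 3/4.8 ≈ 60% of those events past month 36, in one arm only. A shift of this size would more readily need some missed or false calls as well.

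**The case against.** The strongest reply is that local, unmasked recurrence assessment is a design preference in an open-label phase II trial, and that the sentence may simply mean treatment blinding. It closes a paragraph on participant numbers, eCRF access and data collection, and it names neither radiologists nor the statistician. This stands in part. A reader might infer that the protocol expressly bars masked reading, but it does not. It is an unqualified sentence with no exemption anywhere else, and narrowing it costs little under either reading.

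Second, no section says who reads the scans or that the reader is told the arm. Allocation appears on the eCRF page, and only registered researchers have access to that. A hospital radiologist may already be unaware of the arm. This also stands: the point is a risk left open, not a demonstrated bias. It does not remove the point, because nothing in the described process keeps the arm from the reader.

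Third, a reader might infer that every shift in a recurrence date feeds straight into 3-year DFS and can never be undone. The definition of the endpoint does not support the first part. Repeat scheduled imaging gives later chances to call a true lesion, and nothing in the article rules out a later masked re-read of the scans.

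Fourth, masked arm labels for the statistician are often left to an analysis plan, which is not shown, and they protect analysis choices rather than scan reading. For that reason they are offered only as a separate safeguard and carry none of the argument about assessment bias.

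**Conclusion.** The point holds as a risk. The decision not to blind goes further than its stated reason, and the primary endpoint depends partly on judged imaging calls. The size and direction of any bias cannot be known from the documents, and saying that the trial's DFS comparison is biased would go beyond them.

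The figures of 10–14% (two-sided) and 18–23% (one-sided) are conditional. They rest on an assumed net one-way shift of 2 to 3 points, no true effect, 65% DFS in both arms, 156 per arm and a normal approximation. The matching critical differences are about 8.9 and 6.9 points. Using the standard error under the planned alternative, √(0.65 × 0.35/156 + 0.775 × 0.225/156) = 5.1 points, would give smaller thresholds near 8.3 and 6.5. Those do not belong with a false-positive calculation: at the null, an 8.3-point threshold is exceeded by chance about 6% of the time, not 5%.

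This is a worthwhile, low-cost improvement and not a fatal flaw.

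**What to change.** Replace the blinding sentence in Data management with wording such as:

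> Patients and treating investigators are not blinded. Scheduled recurrence imaging is requested and reported without stating the treatment arm, by the radiologist who would read it in any case. The recurrence date is recorded from that report, or from pathology where available. Separately, the statistician works with masked arm labels until endpoint dates and analysis sets are frozen.

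The cost is protocol wording, a line on the imaging request form and an eCRF instruction on the source of the recurrence date. No second or central reader is needed, and the sample size does not change. The unit that runs the randomization program, described in Randomization as independent of the sponsor, could plausibly hold the arm key. According to Trial status, 19 of 312 patients had been enrolled by July 2023, so nearly all recurrence calls still lay ahead at that date.

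Limits: masking is imperfect if the radiologist opens the chart. The change does not touch the investigator's discretion over scan modality and interval in Recurrence assessment, which is a separate route by which knowledge of the arm could act. The wording also does not say how a recurrence first suspected from carcinoembryonic antigen would be dated; the sponsor should settle that in the same amendment.
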